### Statistical methods

Statistical analyses will be conducted based on an intention-to-treat population. Participants who take at least one dose of drug and have one value on treatment comprise the full-analysis set (FAS) and those who complete a 12-week treatment comprise the per-protocol set (PPS). Missing data will be imputed with the use of the last-observation-carried-forward method, whereby missing values will be replaced by the last non-missing value. Repeated measures and multivariate analysis of variance of the general linear model will be applied to determine the changes in GFR, Scr and FPG at each visit. Percentage reduction from baseline in ACR and changes from baseline in HbA1c will be summarized and comparisons will be made by using a one-way analysis of variance.

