### Outcome measures

#### Primary outcome

The primary outcome, percentage change in ACR from baseline, will be measured at week 12. ACR will be measured with a spot urine test, every four weeks; 15 to 20 ml spot urine samples will be collected at each visit to assess albuminuria.

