### Compliance

Establishment of TCM and irbesartan after each visit will be quantified in order to enhance medication compliance. Participants whose compliance with TCM or irbesartan is < 80% of the total dose will be considered to have dropped out.

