### Sample size

Each arm will only include 12 subjects, for this is just a pilot trial aimed at exploring some parameters for a future clinical trial with a large sample size.

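### Carrying a week-4 or week-8 ACR forward as the week-12 primary result can bias the arm comparisons, and the full-analysis set does not fit the intention-to-treat label

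*Protocol article*

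**What the plan says.** All of this comes from the protocol article.

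- **Endpoint and visits (Primary outcome).** "The primary outcome, percentage change in ACR from baseline, will be measured at week 12". Also: "ACR will be measured with a spot urine test, every four weeks". Values at weeks 4 and 8 therefore exist to be carried forward.
- **Missing data (Statistical methods).** "Missing data will be imputed with the use of the last-observation-carried-forward method". No outcome is exempted.
- **Test (Statistical methods).** For ACR and HbA1c, "comparisons will be made by using a one-way analysis of variance". Repeated-measures methods are named for GFR, serum creatinine and fasting glucose, but not for ACR.
- **Population (Statistical methods).** "Statistical analyses will be conducted based on an intention-to-treat population". The next sentence reads: "Participants who take at least one dose of drug and have one value on treatment comprise the full-analysis set (FAS". The per-protocol set is those who complete 12 weeks of treatment. No separate intention-to-treat set is defined.
- **Compliance.** "Participants whose compliance with TCM or irbesartan is < 80% of the total dose will be considered to have dropped out". The section does not say whether ACR values measured in these patients are kept.
- **HbA1c (Secondary outcomes).** It is scheduled at week 12 only, not at the four-weekly visits.

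**The concern.** Last observation carried forward (LOCF) assumes that a patient's ACR stays exactly where it was when last seen. If ACR is still falling or rising, a week-4 or week-8 value is the wrong quantity for a week-12 endpoint, yet the analysis of variance counts it as a real week-12 observation. An arm with more or earlier leavers is then shifted relative to the others.

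Equal dropout does not remove the problem. If all arms lose patients at the same rate, every effect is pulled towards its early value and the differences between arms shrink. That matters for the first objective, which asks whether granule and decoction are equivalent, because shrinkage makes them look alike. It also blurs the dose comparison and the irbesartan comparison.

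The population wording adds a second difficulty. A randomised patient with no on-treatment value belongs to an intention-to-treat population but not to the full-analysis set (FAS). With 12 per arm, each such patient is 1/12 = 8.3% of an arm.

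The trial exists to supply parameters for a larger one, so distorted means and spreads would be passed on to its design.

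**Working it through.** **Inputs from the article:** 12 patients per arm; ACR every four weeks; endpoint at week 12; LOCF; one-way analysis of variance on percentage reduction. The article states no effect size, standard deviation, dropout rate or power, so there is no figure of its own to reproduce. Everything below rests on assumptions, stated as such.

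**1. Linear change, balanced timing.** Assume the mean changes linearly to D = -30% at week 12, so week 4 is -10% and week 8 is -20%. A share d leaves, half after week 4 and half after week 8:

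LOCF mean = (1 - d)D + (d/2)(D/3) + (d/2)(2D/3)

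| d | Calculation | LOCF mean | If all leave after week 4 |
|---|---|---|---|
| 10% | -27 - 0.5 - 1.0 | -28.5% | -28% |
| 20% | -24 - 1.0 - 2.0 | -27.0% | -26% |
| 30% | -21 - 1.5 - 3.0 | -25.5% | -24% |

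**2. Log-linear decline, early leavers in one arm.** Assume a fall to -40% at week 12, with exp(ln(0.6) × w/12) - 1 at week w. This gives -15.7% at week 4 and -28.9% at week 8. Let 3 of 12 leave after week 4.

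- Arithmetic mean, the scale of the planned analysis: (9 × -40 + 3 × -15.7)/12 = -33.9%.
- Geometric mean: (9 + 3/3)/12 × ln(0.6) = -0.426, that is -34.7%. Against an arm with no dropout this is a spurious ratio of 0.653/0.600 = 1.09.
- With 4 of 12 leaving, the geometric mean is -32.8% and the ratio 1.12.

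**3. Equal dropout in both arms.** Under the same log-linear assumption, losing 3 of 12 after week 4 in each arm multiplies the log difference by 10/12 = 0.833. A true ratio of 0.75 becomes exp(0.833 × ln 0.75) = 0.79.

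**4. Simulation.** This used 12 per arm and 8,000 runs per scenario. The assumptions were:

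- between-patient SD of log ACR 0.55, within-patient SD 0.25 or 0.40, SD of individual slopes 0 or 0.3;
- log change by week 12 of 0 or -0.4;
- dropout of 10%, 20% or 30%, either at random or more likely after a poor week-4 response.

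With a falling ACR, LOCF understated the reduction by 1.4 to 8.4 percentage points. With no mean trend, the bias ran from -1.4 to +2.7 points.

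**5. Standard error.** In the same simulations the reported LOCF standard error was:

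- 0.91 to 1.02 times the true sampling SD of the LOCF mean;
- 0.93 to 1.22 times the complete-data standard error;
- 0.80 to 1.09 times the completers' standard error.

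It can be too small: 10.8 against 12.8 at 30% random dropout with no trend. It can also be too large: 8.83 against 8.11 for completers, with a falling ACR and 30% response-related dropout (within-patient SD 0.25, no individual slopes).

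**6. HbA1c.** There is no earlier scheduled on-treatment value. For a patient without a week-12 result, LOCF could only carry a pre-treatment value, which makes the change zero by construction.

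**The case against.** **Standard errors.** A reader might infer that LOCF always makes standard errors too small, for example by sqrt(9/12) = 0.87 when 3 of 12 values are carried. That assumes an unchanged SD, and mixing week-4, week-8 and week-12 values can widen the spread. It also concerns one arm mean. For a contrast at equal SD the ratio is sqrt(2/12)/sqrt(1/9 + 1/12) = 0.93. The simulations show errors in both directions, so the stronger claim is not supported.

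**Dropped patients.** A reader might also infer that the primary analysis certainly discards patients without an on-treatment value. The article never says that the FAS is the intention-to-treat set, and carrying the last non-missing value could mean carrying baseline. What stands is that the label and the definitions do not fit together.

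**Unequal dropout.** The Background calls repeated daily decocting over a long time very difficult. That is the reason for making granules, not a forecast for a 12-week trial. Unequal dropout is possible, not established.

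**Size.** All magnitudes are assumed. The 1.09 ratio is 0.085 in logs. If the SD of log change is 0.3 to 0.6 (assumption), the standard error of a 12-versus-12 contrast is 0.12 to 0.24, so the shift is about 0.35 to 0.7 standard errors.

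**Pilot status.** "Each arm will only include 12 subjects, for this is just a pilot trial aimed at exploring some parameters". This lowers the stakes for testing, but the parameter estimates are the product of the trial, so it does not excuse biasing them.

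**Per-protocol set.** The set of 12-week completers relies little on carried values. It conditions on staying, however, and can err the other way. In the last scenario of step 5 the true mean was -28.7%, LOCF gave -22.1% and completers -32.0%.

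**Unseen analysis plan.** It may add sensitivity analyses, and their absence from an article is not counted here. The choice of LOCF is stated outright, so it is not a detail left open.

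**Conclusion.** The point holds in a limited form. As written, the plan enters week-4 or week-8 ACR as the week-12 primary result for early leavers. If ACR is still changing, this can bias arm means and between-arm contrasts, and it does not properly represent the uncertainty from missing data, in either direction. Under the illustrative assumptions, a true -30% is reported as -28.5% to -25.5% at 10% to 30% dropout, and a true -40% as about -34% to -35% with 3 of 12 early leavers. If few patients leave, or ACR has levelled off by week 4, the effect is small.

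The HbA1c consequence follows directly from the schedule. The mismatch between the intention-to-treat label and the FAS is an inconsistency to resolve; its numerical effect cannot be given from the article. The documents do not establish that standard errors are always understated, that patients are definitely excluded from the primary analysis, or that dropout will differ between arms.

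**What to change.** - **Primary analysis.** Analyse ACR with a likelihood-based repeated-measures model using all observed visits (weeks 4, 8 and 12) without imputation, and report the week-12 contrasts. Include baseline ACR. If it enters as one of the repeated outcomes with a common mean, for example on the log scale, every randomised patient with a baseline is included. A patient with baseline only adds very little to the week-12 contrast. The choice of scale is a separate decision.
- **Population.** Define the intention-to-treat set as all randomised patients and state how the FAS relates to it. Report by arm how many have no on-treatment value.
- **Data.** Continue to collect ACR at the scheduled visits after treatment stops. Use those measured values, including for patients below 80% compliance, so that no observed week-12 result is replaced by a carried one.
- **HbA1c.** Do not carry the pre-treatment value forward as the main analysis.
- **LOCF.** Keep it at most as a sensitivity analysis.

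**Cost.** No extra patients and no new visit dates; revised analysis wording, somewhat more analysis work, and follow-up of patients who stop treatment. The model relies on data being missing at random. That cannot be verified, and post-discontinuation ACR makes it easier to defend.

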### Objective

The aim of this clinical study is: (1) to evaluate if the efficacy of *Huang Qi* Elixir for proteinuria in patients with microalbuminuria is equivalent to that of the decoction; (2) to establish the working dose of the TCM granule; and (3) to evaluate the difference in efficacy between the TCM granule and the ARB (that is, irbesartan).

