### Participants and eligibility

### Inclusion criteria

To be included in the study, patients must have:

1. symptoms of diabetes and a casual plasma glucose ≥11.1 mmol/L or fasting plasma glucose ≥7.0 mmol/L or in a oral glucose tolerance test, two-hour plasma glucose ≥11.1 mmol/L;

2. 30 mg/g < albumin-to-creatinine ratio (ACR) <300 mg/g or 30 mg/24hour <24 hour UAE <300 mg/24 hour, and GFR ≥40ml/min;

3. an age of 18 to 75 years;

4. acceptable glycemic control (FPG ≤10.0 mmol/L or postprandial plasma glucose ≤12 mmol/L and HbA1c ≤8.5%);

5. tolerablity to ARBs and blood pressure (BP) <150/90 mm Hg;

6. plasma albumin ≥30g/L

7. provided written informed consent.

The first two criteria must be met simultaneously.

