#### Secondary outcomes

The secondary outcomes include changes in GFR, Scr, HbA1c, urinalysis and FPG. All of these will be measured every four weeks except for HbA1c, which will be measured at week 12 only.

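### For GFR, Scr and FPG the stated target is change at each visit, with no between-arm contrast named; a baseline-adjusted comparison of arms would be a free improvement

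*Protocol article*

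**What the plan says.** The Secondary outcomes section of the protocol article lists the measures: "The secondary outcomes include changes in GFR, Scr, HbA1c, urinalysis and FPG". On timing it adds: "All of these will be measured every four weeks except for HbA1c, which will be measured at week 12 only". With 12 weeks of treatment, this gives GFR, Scr and FPG a baseline value and values at weeks 4, 8 and 12.

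The Statistical methods section then gives two analyses. For GFR, Scr and FPG it names "Repeated measures and multivariate analysis of variance of the general linear model", which "will be applied to determine the changes in GFR, Scr and FPG at each visit". For percentage reduction in ACR and change in HbA1c the wording is different: "changes from baseline in HbA1c will be summarized and comparisons will be made by using a one-way analysis of variance".

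The Objective section has three aims: whether the granule is equivalent to the decoction, which granule dose to use, and, third, "to evaluate the difference in efficacy between the TCM granule and the ARB". All three compare arms or doses. There are four arms of 12 (two granule doses, decoction, irbesartan) and no placebo arm.

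**The concern.** Two neighbouring sentences give two different targets. ACR and HbA1c are to be compared; GFR, Scr and FPG are to have their changes determined visit by visit. In a repeated-measures general linear model, change at each visit is tested by the visit effect, whose null hypothesis is no change over time. That null can be false when all arms behave identically, and true when arms differ in opposite directions.

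If the visit effect became the basis of inference, a drift common to all patients (from taking part in a trial, from background care, or from entry on threshold values) could be mistaken for an effect of treatment. The second issue is efficiency. If baseline is entered as one of the repeated levels, the model's arm tests are weak: the arm main effect averages a pre-treatment value into the on-treatment ones, and the arm-by-visit test spreads the signal over nine degrees of freedom. In a pilot with 12 per arm, that loss is worth avoiding.

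**Working it through.** **Inputs from the article.** Four arms, 12 per arm, 4 × 12 = 48, which matches the stated total. Visits: baseline and weeks 4, 8 and 12. The article gives no power calculation, so there is no stated operating characteristic to reproduce.

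**Assumed inputs.** Two-sided 5% level; SD 1 at every visit; equal within-patient correlation r = 0.5, 0.7 or 0.85; shared drift 0.2 or 0.3 SD from week 4 onwards. None of these is in the article. Rejection rates below come from the noncentral F distribution with noncentrality λ. Simulation under the same assumptions agrees to within about 3 percentage points.

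**Step 1. Identical arms, shared drift d.** The visit means are 0, d, d, d, and their sum of squares about the mean is 0.75d². For the visit test (3 and 132 df), λ = 48 × 0.75d² / (1 − r).
- d = 0.3: λ = 3.24 / (1 − r) = 6.48, 10.8, 21.6. The visit test rejects in 54%, 78%, 98%.
- d = 0.2: λ = 1.44 / (1 − r) = 2.88, 4.8, 9.6. The visit test rejects in 26%, 41%, 73%.
- The arm-by-visit test has λ = 0 and stays at 5%.

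**Step 2. The same question on one change score per patient.** The drift is now in units of the SD of change. The pooled visit test has λ = 48d² (1 and 44 df). The test within a single arm has λ = 12d² (1 and 11 df).

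| Shared drift (SD of change) | Visit effect, all arms | Change within one given arm | Between-arm test |
|---|---|---|---|
| 0.25 | 40% | 12–13% | 5% |
| 0.5 | 92% | 35% | 5% |
| 0.75 | >99% | 66% | 5% |
| 1.0 | 100% | 88% | 5% |

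Steps 1 and 2 show that the between-arm contrast removes a shared drift. No placebo arm is needed for that.

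**Step 3. Which between-arm test is efficient?** Assume arm effects of +0.4, −0.4, 0 and 0 SD at all three post-baseline visits, with no drift. The sum of squared arm effects is 0.32, and 12 × 0.32 = 3.84.
- Arm main effect, baseline as a repeated level (3 and 44 df): effects shrink to 0.75 × 0.4 = 0.3, so λ = 12 × 2 × 0.09 / [(1 + 3r)/4] = 3.46, 2.79, 2.43. Power 29%, 24%, 21%.
- Arm-by-visit, baseline as a repeated level (9 and 132 df): λ = 3.84 × 0.75 / (1 − r) = 5.76, 9.6, 19.2. Power 31%, 51%, 86%.
- Mean change over weeks 4 to 12, unadjusted (3 and 44 df): variance (1 + 2r)/3 + 1 − 2r = 0.667, 0.40, 0.20, so λ = 5.76, 9.6, 19.2. Power 46%, 70%, 95%.
- Mean of weeks 4 to 12 adjusted for baseline (3 and 43 df): variance (1 + 2r)/3 − r² = 0.417, 0.31, 0.1775, so λ = 9.22, 12.39, 21.63. Power 68%, 82%, 97%. This ignores chance baseline imbalance; simulation gave 65–68%, 79–80% and 97%.

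The visit effect also has power near 5% under this pattern, but that is built in because the arm effects sum to zero. It should not be counted as evidence.

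**The case against.** The strongest reply is that the sentence names a class of model and lists no factors. In a randomised four-arm trial such a model ordinarily carries arm and arm-by-visit terms, and a journal article may leave these to the full protocol or analysis plan. The sentence on one-way analysis of variance does not name arm as its factor either. This stands: a reader might infer that arm is left out, or that visit change will be reported as efficacy, and the article says neither.

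A reader might also infer that the lack of a placebo arm causes the problem. It does not. Contrasts with irbesartan or among the TCM arms cancel a shared drift, and a pooled visit effect would pick up drift even if a placebo arm were present. Without placebo, only the effect against no treatment is out of reach.

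Other parts of the reply also stand. The objectives do not name GFR, Scr or FPG; the first is about proteinuria, which ACR covers. The direction of any drift is uncertain: an upper limit on FPG at entry ("acceptable glycemic control (FPG ≤10.0 mmol/L or postprandial plasma glucose ≤12 mmol/L and HbA1c ≤8.5") would tend to let values rise afterwards, not fall. If the changes at weeks 4 to 12 are themselves the response, the arm effect is not diluted.

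What the reply does not remove is the contrast in wording. The article does state a target for these three outcomes, and it is not the comparison that it states for ACR and HbA1c. One fitted model yields visit, arm and arm-by-visit tests, and naming the model does not say which one carries the inference.

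**Conclusion.** The point holds as a free improvement. For GFR, Scr and FPG the article gives change at each visit as the target and names no between-arm contrast, although its aims compare arms or doses. The text does not support the stronger reading, that the analysis excludes arm differences and will pass off drift as a treatment effect.

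The size depends on assumptions. Under a shared drift of 0.2 to 0.3 SD and r from 0.5 to 0.85, a visit effect would be significant in 26% to 98% of trials with identical arms. Under the assumed arm pattern, adjusting for baseline gains about 22, 12 and 2 percentage points of power over unadjusted change (68 − 46, 82 − 70, 97 − 95), and about 37, 31 and 11 over the arm-by-visit test with baseline as a level (68 − 31, 82 − 51, 97 − 86). The gain is therefore small when correlation is high. Drift, SD, correlation and effect pattern are not in the article.

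The scope is three secondary outcomes in a 48-patient pilot. The primary ACR analysis is not affected.

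**What to change.** Replace the sentence on GFR, Scr and FPG with wording such as: GFR, Scr and FPG at weeks 4, 8 and 12 will be analysed in a repeated-measures model with arm, visit, arm-by-visit and the baseline value as covariate; baseline will not be a repeated level. Inference will rest on between-arm differences at week 12, and averaged over visits, with 95% confidence intervals. Within-arm changes over visits will be descriptive and will not be read as treatment effects.

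The contrasts should follow the Objective section: granule against decoction, one granule dose against the other, and granule against irbesartan.

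The cost is a change of wording before analysis, with no new patients, visits or measurements. The one thing given up is the option of presenting a significant within-arm change as evidence of efficacy.

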### Randomization and intervention

The study has four arms. After enrollment, 48 participants who meet the inclusion criteria will be randomly assigned to either: 1) granule group, 10 grams three times daily (G10 group, n = 12); 2) granule group, 20 grams three times daily (G20 group, n = 12); 3) the decoction group (D group, n = 12); or 4) the irbesartan group (Aprovel group, n = 12). The treatment course is 12 weeks. The randomization sequence will be generated with an SAS software package by the Good Clinical Practice (GCP) Center of the Teaching Hospital of Chengdu University of TCM and will be concealed and disseminated using opaque envelopes.

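### The primary ACR analysis compares percentage change by unadjusted one-way ANOVA: the test is valid, but it is inefficient and the arm means are skewed upward

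*Protocol article*

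**What the plan says.** The Primary outcome section of the Protocol article fixes the endpoint: "The primary outcome, percentage change in ACR from baseline, will be measured at week 12". On measurement it adds: "ACR will be measured with a spot urine test, every four weeks". Statistical methods then says "Percentage reduction from baseline in ACR and changes from baseline in HbA1c will be summarized and comparisons will be made", and on the test: "comparisons will be made by using a one-way analysis of variance". Group is the only factor in a one-way ANOVA, so baseline ACR is not a covariate. The article names no log transformation, geometric mean or rank-based alternative.

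Three other places bear on the point:
- Inclusion criteria admit a tenfold albuminuria range: "30 mg/g < albumin-to-creatinine ratio (ACR) <300 mg/g or 30 mg/24hour <24 hour UAE <300 mg/24 hour".
- Randomization and intervention sets four arms of 12, and Sample size explains the number: "Each arm will only include 12 subjects, for this is just a pilot trial aimed at exploring some parameters for a future clinical trial".
- Objective sets comparative aims, among them "to evaluate the difference in efficacy between the TCM granule and the ARB".

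**The concern.** Percentage change cannot fall below -100% and has no upper limit. Its denominator is a baseline spot-urine value, which is noisy. Three consequences follow.

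- **Arm summary.** The arithmetic mean sits above the change that a typical patient experiences.
- **Influence and spread.** A few large increases can dominate an arm of 12. If a treatment multiplies ACR by some ratio, the standard deviation of percentage change is multiplied by the same ratio, so spread differs between arms whenever treatments differ.
- **Efficiency.** Baseline ACR enters only as the divisor, so the precision that covariate adjustment would bring is not used.

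Two things are at stake: how sharply the arms can be compared with 12 patients each, and the quality of the parameters the pilot hands on. A mean and SD of raw percentage change would carry the skew into the planning of the larger trial.

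**Working it through.** **The plan's own figure.** 4 arms x 12 = 48, as stated. The article gives no alpha, power, effect size or SD, so there is no power figure to reproduce.

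**Asymmetry.** If one patient halves and another doubles, the geometric mean change is 0%, but the arithmetic mean is (-50 + 100)/2 = +25%. In an arm of 12, one fourfold rise (+300%) adds 300/12 = 25 points to the mean. The largest possible fall (-100%) removes only 100/12 = 8.3 points.

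**Closed form for the shift.** If log change is normal with mean 0 and SD s, the mean percentage change is exp(s²/2) - 1. This gives +8.3%, +19.7% and +37.7% for s = 0.4, 0.6 and 0.8.

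**Simulation A.** There were 6,000 trials per scenario, with 4 x 12 patients and an overall test at two-sided 5%. All of the following are assumptions:
- baseline ACR log-normal, centred at 95 mg/g and truncated to 30-300 mg/g;
- log-SD 0.6 or 0.8 before truncation;
- baseline to week-12 correlation 0.5 or 0.7;
- one arm differing from the other three by a fixed ratio.

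With no true change, the rejection rate of the planned ANOVA was 4.2% to 5.1%. In the reference arms the mean percentage change was about +11% to +33%, with a geometric mean change of about 0. Sample skewness was about 1.1 to 1.8.

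Power:

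| Ratio in one arm | log-SD, correlation | % change ANOVA | log-ratio ANOVA | log ANCOVA |
|---|---|---|---|---|
| 0.6 | 0.6, 0.5 | 37% | 54% | 64% |
| 0.6 | 0.6, 0.7 | 64% | 77% | 82% |
| 0.6 | 0.8, 0.5 | 19% | 35% | 40% |
| 0.6 | 0.8, 0.7 | 35% | 53% | 56% |
| 0.5 | 0.6, 0.5 | 63% | 83% | 91% |
| 0.5 | 0.6, 0.7 | 90% | 98% | 99% |
| 0.5 | 0.8, 0.5 | 33% | 60% | 66% |
| 0.5 | 0.8, 0.7 | 60% | 82% | 84% |
| 1.8 | 0.6, 0.5 | 67% | 69% | 77% |
| 1.8 | 0.6, 0.7 | 89% | 89% | 92% |
| 1.8 | 0.8, 0.5 | 39% | 45% | 50% |
| 1.8 | 0.8, 0.7 | 63% | 65% | 69% |

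For reductions, the total gain runs from 8 points (90.3% to 98.6%) to 33 points (33.4% to 66.4%). The log scale supplies about 7 to 26 points of this and the covariate about 1 to 10. For a worsening arm (ratio 1.8), the total gain is about 3 to 11 points.

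**Simulation B.** This is a pairwise contrast with different assumptions: between-patient log-SD 0.6; within-patient log-SD per spot sample 0.3, 0.4 or 0.5; response SD 0.3, 0.3 or 0.4. Separate runs agreed within a few points.
- With no true change, the mean percentage change was about +14%, +21% and +36%, with a median near 0. Type I error was 4.3% to 4.9%.
- For a 40% reduction, power was about 49%, 31% and 20% as planned, against 67%, 52% and 37% with log ANCOVA. The covariate contributed only 0 to 3 points here.

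**What the covariate can give.** On the log scale, before truncation, residual variance relative to a change score is (1 - ρ²)/(2(1 - ρ)) = (1 + ρ)/2. That is 0.75 at ρ = 0.5 and 0.85 at ρ = 0.7.

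**What an arm would report.** With a true ratio of 0.6, the expected arithmetic mean is 0.6 x (1 + m) - 1, where m is the upward shift. For m = 0.11 this is -33%, and for m = 0.33 it is -20%, against a geometric change of -40%. The difference from a reference arm is 0.4 x (1 + m), or 44 to 53 percentage points.

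**The case against.** The strongest reply is that the article never says untransformed. A back-transformed log ratio is also a percentage change, and a condensed article may leave the scale to an analysis plan. This has some force, because most of the gain for reductions comes from the scale. But the untransformed reading is the natural one for a percentage reduction compared by ANOVA, and naming a one-way ANOVA does exclude a baseline covariate.

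A reader might go further and infer that the comparison is biased or invalid. The documents and the checks do not support that. With no true change, the upward shift has the same expectation in every randomised arm, so it creates no spurious difference between arms, and type I error holds near 5%. The arithmetic mean is a legitimate but less useful summary; it does not misestimate itself.

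A reader might also infer a power loss for all three objectives. Only superiority-type differences were examined. The equivalence of granule and decoction was not, and the documents give no basis for expecting 40-50% differences between active arms. The pilot claims no power, so no stated figure is wrong.

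Two limits also stand. Entry on 24-hour UAE is allowed as an alternative, so baseline ACR need not lie within 30-300 mg/g as the simulations assume. And no variance or correlation for ACR appears in the documents.

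**Conclusion.** The point holds as one of efficiency and reporting, not validity. Under the assumed variances, the planned arm mean sits about 11 to 36 points above a geometric mean change of zero. The planned test gives up roughly 8 to 33 points of power for a 40-50% relative reduction in one arm, and about 3 to 11 points if an arm worsens. The direction was the same in every scenario with a true effect; the size depends on the assumptions. The trial being a pilot removes any claim of underpowering against a stated target. It does not remove the interest in a better analysis, since the aims are comparative and the results are meant to inform a larger trial.

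**What to change.** In Statistical methods, replace the ACR part of the one-way ANOVA sentence. Analyse log week-12 ACR by ANCOVA with arm and log baseline ACR. Report the back-transformed percentage change in geometric mean for each arm, and the percentage differences between arms with 95% confidence intervals. For planning the later trial, also report the residual SD on the log scale.

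The cost is one paragraph, with no new data, visits or patients, and the endpoint keeps its name. The small downside is that results become geometric mean ratios, which are not directly comparable with arithmetic mean percentage changes reported elsewhere. Adjusting the HbA1c comparison for its baseline is optional; neither skew nor power was examined for it.
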